| Duration: | According to the product information, the duration of the combination therapy with ribavirin (Copegus®) for chronic hepatitis C depends on the virus genotype. Naive patients with virus genotype 1 and genotypes 2/3 should be treated for 48 weeks and 24 weeks, respectively. Patients with low viral load at baseline (< 800,000 IU/ml) and Rapid Viral Response (HCV-RNA undetectable after 4 weeks of treatment), can sufficiently be treated for 24 weeks only, in case of genotype 1, and for 16 weeks only, in case of genotypes 2/3.  This recommendation is identical for patients with genotype 4.  Duration of retreatment in patients who have failed prior therapy should be 48 weeks in general. In case of genotype 1 patients with prior non-response, retreatment duration of 72 weeks is recommended.  The recommended duration of Pegasys monotherapy is 48 weeks.  In clinical studies with peg­interferon alfa-2a (Pegasys®) alone or in combination with ribavirin (Copegus®) (see product information), a Rapid Viral Response was defined by a HCV RNA load below the limit of detection after 4 weeks of therapy whereas an early virological response was defined by a HCV RNA load below the limit of detection or by a reduction of the virus titre by 99 % of the initial value after 12 weeks of therapy.  Of patients with genotype 1 or 4 and no early virological response after 12 weeks therapy with peg­interferon alfa-2a (Pegasys®) alone or in combination with ribavirin (Copegus®), only a very small number (<2%) achieved sustained virological response.  In those patients, therapy should be discontinued, taking into account the low probability of a sustained virological response.  In patients with genotype 2 or 3, early virological response is known to be very high (97 %) and subsequently a high SVR rate is achieved after 24 weeks. Therefore, viral load determination after 12 weeks of treatment is not deemed to be necessary.  Planned FPI: 01/01/2008  Planned LPI: 31/12/2011  Planned LPO: 30/06/2013 |

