#### Examination after 2 weeks

- Laboratory parameters
  GPT (=ALT), GOT (= AST), GGT
  Other laboratory parameters:
  hemoglobin, platelets, WBC, neutrophils (%), bilirubin
- Adverse events (including suspected cases) with substance-specific causality survey
- Date and dosage information for peg­interferon alfa-2a (Pegasys®): 180 µg and ribavirin, e.g. Copegus® (including dose changes and rationale for change, dose schedule)
- Concomitant medication
- New comorbidities
- Clinical symptoms: none, fatigue, fever, muscular stiffness, skin changes, hair loss, joint pain, muscle pain, abdominal pain, nausea, reflux, weight loss, headache, insomnia, irritability, restlessness, depression, depressive mood, psychosis, impaired concentration, anorexia, jaundice, pruritus, elevated GPT, craving / withdrawal-like symptoms, other;
  causal relationship with Pegasys and/or ribavirin
- Treatment-related sick leave (duration) since the last examination
- Pregnancy test

#### Examinations during treatment in week 4, 8, 12, 24, 36 and 48

- *Only in week 12, 24, 36 and 48:* body weight
- Laboratory parameters
  GPT (=ALT), GOT (= AST), GGT,
  Other laboratory parameters:
  hemoglobin, platelets, WBC, neutrophils (%), bilirubin, creatinine
  *Only in week 12, 24, 36 and 48*: TSH, blood glucose (fasting), HbA1c*Only in week 24:* ANA, LKM, SMA, AMA, SLA, Trak, MAK, rheumatoid factors
- Hepatitis laboratory diagnostic tests
  HCV-PCR (quantitative/qualitative), *in week 4 and 12 recommended*
  HCV-PCR (qualitative), *only in week 24* for GT-2/3, o*nly in week 48 for GT-1/4 recommended*
  (HCV-PCR (quantitative/qualitative) can be documented in week 4, 8, 12, 24 and 48)
- Adverse events (including suspected cases) with substance-specific causality survey
- Date and dosage information for peg­interferon alfa-2a (Pegasys®): 180 µg and ribavirin, e.g. Copegus®: (including dose changes and rationale for the change, dose schedule)
- Concomitant medication
- New comorbidities
- Clinical symptoms: none, fatigue, fever, muscular stiffness, skin changes, hair loss, joint pain, muscle pain, abdominal pain, nausea, reflux, weight loss, headache, insomnia, irritability, restlessness, depression, depressive mood, psychosis, impaired concentration, anorexia, jaundice, pruritus, elevated GPT, craving / withdrawal-like symptoms, other;
  causal relationship with Pegasys and/or ribavirin
- Treatment-related sick leave (duration) since the last examination
- (Monthly) pregnancy test

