#### At the end of treatment / documentation (end of therapy):

- Therapeutic consequence: reason for end / discontinuation of therapy
- Reasons for therapy discontinuation: lacking virological response, lacking tolerability, lacking compliance, unplanned event (e.g. imprisonment, detoxification), patient's wish, patient no longer attended, other reason
- Concomitant medication
- New comorbidities
- Body weight
- Hepatitis C laboratory diagnostic tests
  HCV-PCR (quantitative/qualitative), *only recommended in week 12*
  HCV-PCR (qualitative), *only recommended in week 24 for GT-2/3, only in week 48 for GT-1/4*
  (HCV-PCR (quantitative/qualitative) can be documented in week 4, 8, 12, 24 and 48)
- Hepatitis B laboratory diagnostic tests (only if chronic hepatitis B was documented at the baseline examination): HBsAg (+/-), HBeAg +/-; HBV-DNA quant./qual., anti-HBs (+/-); anti-HDV (+/-), HDV-RNA (+/-, qual. or quant.)
- Autoantibodies: ANA, LKM, SMA, AMA, SLA, Trak, MAK, rheumatoid factors, other
- Laboratory parameters
  GPT (=ALT), GOT (= AST), GGT,
  Other laboratory parameters:
  hemoglobin, platelets, WBC, neutrophils (%), bilirubin, creatinine, TSH, blood glucose (fasting), HbA1c, triglycerides, cholesterol, HDL, LDL, serum ferritin
- Clinical symptoms: none, fatigue, fever, muscular stiffness, skin changes, hair loss, joint pain, muscle pain, abdominal pain, nausea, reflux, weight loss, headache, insomnia, irritability, restlessness, depression, depressive mood, psychosis, impaired concentration, anorexia, jaundice, pruritus, elevated GPT, craving / withdrawal-like symptoms, other;
  causal relationship with Pegasys and/or ribavirin
- Treatment-related sick leave (duration) since the last examination
- (Monthly) pregnancy test
- Adverse events (including suspected cases) with substance-specific causality survey
- Clinical assessment of the tolerability of Pegasys and the combination with ribavirin (Copegus®): very good, good, moderate, poor
- Quality of life assessment compared to before treatment: symptom-free; improved, but not symptom-free; unchanged
- Alcohol consumption no/yes, if yes, inquiry ≤/ > 40 g/d and drinks/d in the last 30 days
- Compliance (assessed by the physician):
   very good: all medications taken
   good: max. 10% not taken
   satisfactory: max. 20% not taken
   poor: > 20% not taken
- Quality of life assessment compared to before treatment: symptom-free; improved, but not symptom-free; unchanged

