## Analysis plan

The descriptive statistical evaluation is performed by the company factum GmbH.

All recorded data – depending on the type of characteristics – are presented descriptively as mean, standard deviation, minimum, maximum, median, 1st and 3rd quartile or their frequency distribution. Categorical characteristics are presented with absolute and relative frequencies within the individual categories.

For continuous variables multiply recorded over time, basic statistics with absolute differences between the end of observation and the baseline value are calculated.

For the tolerability analysis, adverse drug reactions are counted by frequencies using the respective preferred terms categorized according to organ systems. These survey tables are additionally stratified according to the clinical relevance of the drug effect as "serious/non-serious".

Moreover, an assessment of the clinical tolerability of the hepatitis C therapy is performed by the physician.

For the safety laboratory analysis, basic statistics over time are generated per parameter. Additionally, the frequencies of changes in categorical laboratory values (classified into "normal", "increased", "reduced") are presented per laboratory parameter between the baseline value and end of treatment and between the end of treatment and follow-up.

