# Report

At the latest 12 months after the end or premature termination of the noninterventional study, a written report is generated. This report contains:

- number of patients enrolled in the study
- number of participating centres
- descriptive presentation of all recorded observational variables
- checking of the representativeness of the included centres and patients
- presentation of the effect of interfering variables and their importance for interpretation of the results
- Assessment of the results in relation to the previous recommendations for treatment
- General assessment of the study

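### The three-class laboratory change table in section 8.3 cannot show same-direction worsening, degree of abnormality, or extremes that recovered by end of treatment

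*Protocol*

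**What the plan says.** Protocol section 8.3 (Analysis plan) names two safety laboratory outputs. The first is general: "For the safety laboratory analysis, basic statistics over time are generated per parameter". The second is the change table: "the frequencies of changes in categorical laboratory values (classified into 'normal', 'increased', 'reduced", compared "between the baseline value and end of treatment and between the end of treatment and follow-up". So the section fixes both the classes (three, ungraded) and the intervals (two).

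Other parts of the plan bear on the same question:

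- Section 8.3 also plans summary statistics of the absolute difference between baseline and end of observation for continuous variables measured repeatedly.
- Section 9 (Report) promises a "descriptive presentation of all recorded observational variables".
- Section 7.4 makes an abnormal laboratory value an adverse event if it is symptomatic, changes treatment, needs intervention or is judged clinically relevant. Section 7.2.8 records severity for each adverse event.
- Section 7.2.2 provides laboratory fields at baseline, at week 2, at the "Examinations during treatment in week 4, 8, 12, 24, 36 and 48", at end of treatment and at week 24 of follow-up. The week 4 to 48 list includes "hemoglobin, platelets, WBC, neutrophils (%), bilirubin, creatinine"; the end-of-treatment list begins "hemoglobin, platelets, WBC, neutrophils (%), bilirubin, creatinine, TSH, blood glucose (fasting), HbA1c". GPT is on all of these forms. Creatinine is not listed at week 2.

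**The concern.** Safety is part of the main objective in the Synopsis, and section 4.2 wants the safety data compared with the known profile. A reader of the report will want to know how many patients reached each degree of, say, anaemia or neutropenia, and from what starting point.

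The change table is the only stated laboratory output that follows patients from one category to another, and it has three limits:

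1. A value already reduced or increased at baseline has no worse class in that direction.
2. A new abnormality falls in the same cell whatever its size.
3. The only treatment-period value used is the one at end of treatment, so an extreme that has recovered by then is not shown.

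The protocol foresees the relevant situations. Elevated GPT is among the listed findings that may lead to diagnosis (section 7.2.2), so some patients may start in the increased class. Section 7.4 foresees dose adjustment or interruption for abnormal values, after which a low value may recover before end of treatment.

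**Working it through.** The plan states no figure to reproduce. The check is what the table's rule does to patient courses, and how many values it uses.

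**Cells.** Three classes at two times give 3 × 3 = 9 cells. Two of them (reduced to reduced, increased to increased) hide same-direction worsening. Four (normal to reduced, increased to reduced, normal to increased, reduced to increased) pool all degrees of the new abnormality. Crossings between reduced and increased are counted.

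**Example courses.** The protocol gives no reference limits. For illustration I assume a GPT upper limit of 50, haemoglobin 13 to 17 g/dl and platelets 150 to 400. Other limits would change the examples but not the pattern.

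| Course | Table entry, baseline to end of treatment |
| --- | --- |
| GPT 80, end of treatment 400 | increased to increased |
| Platelets 120, end of treatment 30 | reduced to reduced |
| Haemoglobin 14, end of treatment 12.5 | normal to reduced |
| Haemoglobin 14, end of treatment 7 | normal to reduced |
| Haemoglobin 14, low point 8, end of treatment 13.2 | normal to normal |
| GPT 80, flare 600, end of treatment 45 | increased to normal |

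The first two show no change, the next two share a cell, and the last two hide the event (the GPT flare reads as improvement). A worst-value table with the same three classes would expose the haemoglobin low point of 8. It would still miss the first two courses and would not separate 12.5 from 7. Grades and the worst value are therefore both needed.

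**Values provided for.** Forms are at weeks 2, 4, 8, 12, 24, 36 and 48 (section 7.2.2), plus end of treatment. Course lengths come from the Synopsis (Duration) and section 4.1.3. These give 48 weeks as standard for genotype 1 and 24 for genotypes 2/3, with low-viral-load rapid responders who "can sufficiently be treated for 24 weeks only, in case of genotype 1, and for 16 weeks only, in case of genotypes 2/3". They also give 72 weeks for some retreatments, and a stop at week 12 without early virological response in genotypes 1 and 4.

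| Course | Forms counted | Values | Creatinine |
| --- | --- | --- | --- |
| Stop at week 12 | 2, 4, 8 + end (week 12 if separate) | 4 to 5 | 3 to 4 |
| 16 weeks | 2, 4, 8, 12 + end | 5 | 4 |
| 24 weeks | 2, 4, 8, 12 + end (week 24 if separate) | 5 to 6 | 4 to 5 |
| 48 weeks | 2, 4, 8, 12, 24, 36 + end (week 48 if separate) | 7 to 8 | 6 to 7 |
| 72 weeks | all seven + end | 8 | 7 |

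The table uses one of these. If all were taken, the share not entering it is 3/4 = 75% to 7/8 = 87.5% (creatinine 2/3 = 67% to 6/7 = 86%). The counts are maxima, because sections 4.3 and 7.2 leave testing to the physician. A patient who stops earlier than week 12 has fewer.

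**Other outputs, set against the three limits.** Statistics over time use every visit. Their minimum and maximum show that an extreme occurred, but not in how many patients or from what baseline. Absolute differences do register GPT 80 to 400 (+320) or platelets 120 to 30 (-90) if still present at end of observation, but only inside a group summary and only at that final time. Adverse events capture recovered extremes that meet a section 7.4 criterion, with severity. However, the 8.3 tables count adverse drug reactions and split them only by seriousness.

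**The case against.** The strongest reply is that nothing here is wrong. The table is computable, is introduced as an addition to the statistics over time, and does not exclude further outputs. Toxicity grading and worst-value tables often sit in a statistical analysis plan, and that document is not at hand. This stands as a limit on weight. It does not remove the point, because section 8.3 itself fixes classes and intervals, and a later plan that only follows it inherits the three limits.

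A reader might infer that the safety analysis as a whole is blind to worsening or to recovered events. The documents do not support that. A low value corrected by dose change or by treatment meets a section 7.4 criterion by definition, its severity is recorded, and the report is to describe all recorded variables. Within-patient differences from baseline are also summarised. What stays uncovered is the count of patients by laboratory grade against baseline, above all for abnormalities that met no adverse event criterion.

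It is also tempting to read the 75% to 87.5% as data thrown away. It is not: those values still enter the statistics over time.

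A further objection is that a worst value depends on how often a patient is tested. This is true. If each value independently has chance q of being severe, the worst of k values is severe with chance 1 - (1 - q)^k:

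| q (assumed) | k = 2 | k = 5 | k = 8 |
| --- | --- | --- | --- |
| 1% | 2.0% | 4.9% | 7.7% |
| 2% | 4.0% | 9.6% | 14.9% |
| 5% | 9.8% | 22.6% | 33.7% |

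Reporting the number of values shows this dependence but does not remove it, particularly if sicker patients are tested more. For unscheduled tests, section 7.2.7 records only how many were done, so the true low point may be missed. These are reasons to read the table as descriptive, not reasons to leave it out.

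Finally, grading needs reference limits from many centres. So does sorting values into normal, increased and reduced; no new requirement arises.

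**Conclusion.** The point holds for the categorical change table and no further. By construction, whatever the reference limits, that table cannot count same-direction worsening, pools mild with severe new abnormalities, and does not show extremes that recovered by end of treatment. An abnormality still present at end of treatment does appear. The table draws on one of about 4 to 8 treatment-period values per patient (3 to 7 for creatinine), assuming the described course lengths and complete testing.

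How many patients this affects cannot be derived from the document, so no claim about the number of missed severe events is justified. The weight is low: a useful addition to a stated method, not a correction of an error.

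**What to change.** Keep the planned table and add to section 8.3, for haemoglobin, platelets, WBC, absolute neutrophils (WBC × neutrophil % / 100), GPT, bilirubin and creatinine:

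- a shift table from baseline grade to worst documented on-treatment grade, week 2 to end of treatment;
- a shift table from baseline grade to end-of-treatment grade.

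Use one toxicity scale with ordered grades (for example CTCAE, version fixed before analysis) and the same reference limits that the three-class table needs. Show GPT also as a multiple of the patient's baseline value. With each table report the number of patients with paired values and the distribution of the number of on-treatment values per patient. State that the worst-grade table is descriptive, depends on testing frequency and does not contain the results of unscheduled tests.

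The cost is a few sentences, some programming and larger tables. No new visits or measurements are needed, because section 7.2.2 already provides for the values.

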# Report

At the latest 12 months after the end or premature termination of the noninterventional study, a written report is generated. This report contains:

- number of patients enrolled in the study
- number of participating centres
- descriptive presentation of all recorded observational variables
- checking of the representativeness of the included centres and patients
- presentation of the effect of interfering variables and their importance for interpretation of the results
- Assessment of the results in relation to the previous recommendations for treatment
- General assessment of the study

# Administrative aspects

## Ethical advice

An expert assessment of the noninterventional study by the ethics committee is planned. The Scientific Director submits the observational protocol together with the informed patient consent document to his competent ethics committee for deliberation. Every participating physician can also receive ethical advice from his/her competent ethics committee on the basis of his/her professional obligation. The observational protocol together with the patient informed consent document can be passed on for this purpose.

The ethical consultation provided by the ethics committee is intended to ensure, among other things, that patient rights are not compromised and that the noninterventional study is designed for adding to existing knowledge.

## Legal principles and registration

The present survey is a noninterventional study pursuant to Section 4 Subsection 23 of the German Medicines Act (AMG) and is registered by Roche with the higher federal authority, the National Association of Statutory Health Insurance Physicians (KBV) and the Head Association of the Statutory Health Insurance Scheme (GKV) in accordance with Section 67 Subsection 6 AMG. The location, time and purpose of the noninterventional study is stated and the observational protocol is included. The involved physicians are identified by name to the KBV and Head Association of the GKV and a copy of the specimen agreement between Roche and the participating physicians is forwarded to the KBV and the Head Association of the GKV.

Information about the nature and amount of the compensation provided as required by Section 67 Subsection 6 AMG is forwarded, together with the report of the conclusion of the NIS, to the KBV and the Head Association of the GKV.

Roche has obtained agreement to this measure from the participating physicians on a contractual basis.

## Quality assurance measures

### Monitoring

The availability of an informed consent form signed by the patient is the precondition for the transmission of pseudonymized data. To verify that this precondition is fulfilled, authorized representatives of Roche Pharma AG may when necessary inspect this declaration of informed consent, which otherwise remains with the treating physician.

In addition, the data recorded for about 5 % of the documented patients is checked by a monitor appointed by Roche by comparing the data entered in the case record forms with the data in the patient file. The patient will be informed of this fact before participating in the noninterventional study and will be requested to give his/her consent. Only patients who have given their consent can be observed in the noninterventional study.

### Data management

The completed case record forms are checked by the commissioned institute for completeness, plausibility and adverse events. The participating physician undertakes to provide all necessary background information to his/her records on request. This is particularly important if data transfer errors are suspected.

Any questions will then be clarified by consulting the physician. The clarification of discrepancies will be documented.

The participating physician assures that the recorded details correspond to the truth.

### Archiving

The physician is responsible for the retention and archiving of all documents of the observational study for the duration of at least 10 years.

If the documentation is to be transferred to another party or to a different location for retention, Roche is to be informed of this fact by the physician in advance.

## Public study registry and publication

The noninterventional study is published in a public study registry prior to its commencement. The summary of results is to be published at the latest one year after completion (last patient / last visit) of the noninterventional study (e.g. publication and presentation at scientific congresses). This is done in consultation between the Scientific Director of the noninterventional study and Roche Pharma AG. However, this does not mean that either of the partners has the right to censor or withhold the publication.

# Reimbursement and fees

Reflecting the nature of the noninterventional study (observational study), the costs of the prescribed product and the medical services are reimbursed by the usual funding agencies as part of routine treatment. The fee for the noninterventional study is therefore to be understood exclusively as reimbursement for recording of the data. The complete documentation of the treatment data of a patient who can be documented in all modules based on the severity of his/her disease is reimbursed with 1,695.34 Euros. The fee can only be paid if the data made available are evaluable under the terms of this observational protocol.

The basis for calculation are reimbursement codes 80 and 85 of the Statutory Scale of Fees for Physicians; code 80 (EUR 17.49) is applied for a documentation effort of up to 20 minutes, whereas from a time input of 20 minutes onwards, reimbursement code 85 (EUR 29.14 for every started hour) applies. An increase factor of up to 2.3 can be applied to the codes depending on the estimated time required for the documentation.

The total amount for the complete documentation of a patient is calculated by adding up the complete documentation for the various visits in the main module hepatitis and the respective secondary modules HIV coinfection, opioid substitution, cardiovascular risk, liver transplantation and pharmacoeconomics. The assessment of the individual visits is shown in the following table.

| Module | Hepatitis | GÖA* | Factor | HIV infec-tion | GOÄ | Fac-tor | Opioid sub-stitution | GOÄ | Fac-tor | Cardio­vascular risk | GOÄ | Fac-tor | Trans­plan­ta­tion | GOÄ | Factor | Pharma­co-economics | GOÄ | Factor |
| --- | --- | --- | --- | --- | --- | --- | --- | --- | --- | --- | --- | --- | --- | --- | --- | --- | --- | --- |
| Baseline examination | 67.02 | 85 | 2.3 | 67.02 | 85 | 2.3 | 34.98 | 80 | 2 | 20.11 | 80 | 1.15 | 67.02 | 85 | 23 |  |  |  |
| Week 2 | 29.73 | 80 | 1.7 |  |  |  | 127.49 | 80 | 1 |  |  |  |  |  |  | 22.74 | 80 | 1.3 |
| Week 4 | 34.98 | 80 | 2 |  |  |  | 127.49 | 80 | 1 |  |  |  |  |  |  | 22.74 | 80 | 1.3 |
| Week 8 | 34.98 | 80 | 2 |  |  |  | 127.49 | 80 | 1 |  |  |  |  |  |  | 22.74 | 80 | 1.3 |
| Week 12 | 58.28 | 85 | 2 | 34.98 | 80 | 2 | 17.49 | 80 | 1 |  |  |  | 58.28 | 85 | 2 | 22.74 | 80 | 1.3 |
| Week 24 | 58.28 | 85 | 2 | 34.98 | 80 | 2 | 24.49 | 80 | 1.4 | 20.11 | 80 | 1.15 | 58.28 | 85 | 2 | 22.74 | 80 | 1.3 |
| Week 36 | 58.28 | 85 | 2 |  | 80 | 2 | 17.49 | 80 | 1 |  |  |  | 58.28 | 85 | 2 | 22.74 | 80 | 1.3 |
| Week 48 | 58.28 | 85 | 2 | 34.98 | 80 | 2 | 24.49 | 80 | 1.4 | 20.11 | 80 | 1.15 | 58.28 | 85 | 2 |  |  |  |
| End of treatment | 67.02 | 85 | 2.3 | 34.98 | 80 | 2 | 24.49 | 80 | 1.4 | 20.11 | 80 | 1.15 | 58.28 | 85 | 2 | 22.74 | 80 | 1.3 |
| W24 follow-up | 67.02 | 85 | 2.3 | 34.98 | 80 | 2 | 24.49 | 80 | 1.4 | 20.11 | 80 | 1.15 | 58.28 | 85 | 2 | 22.74 | 80 | 1.3 |
| **Total** | **533.88** |  |  | **241.92** |  |  | **220.37** |  |  | **100.57** |  |  | **416.70** |  |  | **181.90** |  |  |
| **Max. total per  patient** | **1695.34** |  |  |  |  |  |  |  |  |  |  |  |  |  |  |  |  |  |

* German Scale of Statutory Fees for Physicians

For incompletely documented visits that cannot be used for the evaluation under the terms of the observational protocol, relevant queries are submitted to the participating physicians through the query management that make it possible to fully present and complete the visits. If no complete documentation of a visit is achieved, the documentation is not reimbursed.

Since on the one hand prompt documentation is required and on the other hand it is usually impossible to document data electronically during a patient visit in addition to maintaining the patient file, it is advisable first to document the data in a hardcopy version of the case record form and then to transfer this version to the electronic CRF later on. Transfer to the electronic CRF can be delegated by the participating physician to a study assistant. The contracting party can contractually assign 20 % of the documentation fee to the study assistant for this purpose. 80 % of the total fee amount then remains for the contracting party. (For administrative reasons, agreement to a change in the percentage distribution between the contracting party and the study assistant is only granted in justified exceptional cases and after the agreement of the medical manager or one of his representatives.)

For the documentation of the prescribed HIV concomitant medication in the pharmacoeconomics part, a documentation effort of EUR 34.98 is reimbursed with a factor of 2 in accordance with the statutory fees for physicians.

For the documentation of the prescribed substitution medication in the pharmacoeconomics part, a documentation effort of EUR 17.49 is reimbursed with a factor of 1 in accordance with the statutory fees for physicians.

The practice characteristics can be documented once per calendar year. A documentation effort of EUR 20.11 is reimbursed for this with a factor of 1.15 in accordance with GOÄ 80. Whether this amount is reimbursed to the participating physician or study assistant is regulated in the contract concerning the performance of the NIS.

For the administration and explanation effort required for the quality of life questionnaires SF36 to be completed by the patient and the sociodemography questionnaires at 4 time points during the therapy (baseline examination, week 12, end of treatment/documentation, week 24 follow-up), a reimbursement amount of EUR 2.50 is paid per form, i.e. EU 10.00 for one complete set of questionnaires per patient. Whether this amount is reimbursed to the participating physician or the study assistant is regulated in the contract concerning the conduct of the NIS.

